**Figure 2 F2:**
[figure not shown]
Abridged CONSORT diagram.

### Intervention description

#### Experimental group

Dyads included in the ACCOMPAGNE educational program group will take part in seven collective workshops, spread over three half-days (once a week for three consecutive weeks). Each workshop lasts approximately an hour and a half and uses educational content and pedagogical methods. Materials and methods of each workshop are described in Table 1.

**Table 1 T1:** ACCOMPAGNE program workshops.

**Workshop (duration)**	**Main objective and methods**	**Materials (example)**
Workshop introduction (1 h)	Main objective: To increase participant's involvement by considering him/her as a key member of the workshops and to initiate a group dynamic.	
	Method: Round table: each participant answers the questions on the “question wheel”: Name, first name, age, place of residence. Do you like to drive? Do you drive often? For which activities? Do you experience any difficulties when driving? Motor skills? Concentration? Memory problems?	
Cognitive skills workshop (1h30)	Main objective: to facilitate awareness of the cognitive skills involved in driving (visuo-spatial, attentional, memory, executive).	[figure not shown]
	Method: After defining the different cognitive mechanisms involved in driving, role plays are distributed. The participants have to imagine the cognitive mechanisms involved in each situation.	
Perception and environment workshop (1h30)	Main objective: To facilitate awareness of sensorimotor skills required to drive safely.	[figure not shown]
	Method: For each visual skill (acuity, accommodation, contrast and distance vision) the facilitator creates a discussion around the questions “What role does this skill play in driving? What is the risk if this skill is impaired?” Establishment of a checklist based on sensory status and level of alertness green light = safe driving/orange = adaptation required/red = do not drive	
Driving responsibilities workshop (1 h30)	Main objective: To facilitate awareness of accident risks linked to a driving affected by cognitive disorders or illness. To facilitate awareness of one's own responsibilities as a driver.	“Mrs. A., 82 years old, attends memory clinic for cognitive disorders and attentional difficulties. She also has a cataract. She uses her car several times a week to do her shopping. On this particular day, it is raining. Mrs A has to turn right, she does not see the bicycle that was riding behind her and hits it. The cyclist is injured and apparently has a broken arm. The cyclist is taken to hospital by the fire brigade and will probably need an operation.” What do you think are the administrative steps to be taken for Mrs A.?
	Method: Reflection on situation vignettes. What are the responsibilities? Does she need to have her driving assessed? In the long term, what steps can she take to assess her driving?	
Patient workshop (1 h)	Main objective: To share personal experience with driving and with driving adjustments because of cognitive or sensory disorders.	[figure not shown]
	Method: Patients are asked to write 8 words or short sentences on 8 post-its (one idea per post-it) around the question “What are the abilities needed to drive safely? A collective meta-plan is made to synthesize all the ideas. Each patient then chooses a photo. The psychologist allows the patients to discuss their representations, and relies on the sharing of experiences to soften the impact of giving up driving.	
Caregiver workshop (1 h) (at the same time than representation workshop)	Main objective: To allow speaking time to the caregivers so they can ask the questions they cannot ask when their relative is present.	[figure not shown]
	Method: Envelope method. The natural caregivers ask their questions freely. The facilitators write down each question on a different envelope. Each participant will have to provide solutions to the questions in each envelope in turn (based on their own experience or on information acquired in the previous workshops). A collective discussion then allows the proposed solutions and possible adaptations to be listed.	
Driving strategies and alternatives workshop	Main objective: To establish required strategies or means for safe and autonomous driving.	
	Method: Presentation of risky situations (Night driving, rush hour, city traffic, unfamiliar or long routes, intersections, roundabouts, bends, insertions, difficult weather conditions, motorways, telephones, radio, chatter, physical pain, drunkenness, emotional stress..) and group discussion on possible solutions or alternatives (avoidance, adaptations like turn off the radio in challenging situations, planning the journey ahead of time…). Brainstorming about resources that can be used to avoid some driving situations and making a dyad specific alternative transportation plan.	

A neuropsychologist begins by introducing the program and explains the educational objectives in the *Introductory workshop*.

The neuropsychologist then proposes the *Cognitive skills workshop*. The objective is to help participants and their caregivers to understand the main cognitive functions and behavioral skills (self-control, stress management, compliance with instructions) involved in driving activity. The material provided for this workshop consists of photographs showing several driving situations which are known to be complex for older individuals (heavy traffic, unexpected events, dangerous intersections). The material will help individuals to think about the cognitive functions involved in driving activity, and to better understand the impact of these functions on driving activity. Participants are invited to think about the consequences of cognitive disorders in each of these situations. At the end of the workshop, participants ask any questions they might have, and explain their position regarding the continuation of driving activity.

Next, a physician or a nurse introduces the *Perception and environment workshop*. The objective is to help participants to be aware of the sensorimotor skills needed for safe driving (visual, auditory, motor, gestural skills, proprioception). For each skill (visual acuity for distance and near visual field sensitivity to glare, contrast vision, auditory skills, balance and proprioception functions, motor skills and gestures), participant groups determine the impact of aging and of the main age-related diseases. In this workshop, the effects of medication on driving are discussed, as well as anything else that can impact alertness at the wheel (fatigability, drowsiness). Participants are asked to classify each skill based on their personal situations as either green lights (no risk identified), vigilance points, or red lights (identified danger), and to list the possible actions needed to avoid any risks related to impaired skills (for example, avoiding driving at night).

In the following stage the physician presents the *Responsibilities workshop*. The objective is to help participants to put themselves in the position of a responsible driver, and to fully understand the responsibilities of everyone involved in a given situation. A brainstorming method is used. Stories are presented. These feature characters in driving situations in which their responsibility is involved. Participants are then asked questions. A number of legal aspects are discussed, particularly those related to medical conditions which result in an inability to drive. The procedure for responding to a certified physician, the responsibilities of each person, the legal obligations of health professionals and personal obligations relating to the driver and the vehicle are all described and detailed. The procedures used to assess their fitness to drive are also presented.

A psychologist then goes on to present the *Patient workshop*. The objective is to provide a listening place for participants only. Representations, fears, projections related to driving and cessation are discussed. The photo language method is used. Participants are invited to express the value they place on driving, and their feelings about a possible cessation.

At the same time another psychologist presents the *Caregiver workshop*. The objective is to provide a listening place for caregivers only. Questions related to the procedure involved in the fitness to drive assessment, to anosognosia or defensive positions, and to their relative's potential opposition to giving up driving are all discussed. This workshop also presents the attitudes that should be adopted and the adaptive measures that can be implemented.

An occupational therapist or a nurse holds a *Driving strategies and alternatives workshop*. Risky driving situations will be presented to the participants and they will discuss, in the group, about possible solutions or alternatives to such situations (avoidance but also other adaptive strategies like turn off the radio in challenging situations, planning journeys ahead of time…). Participants identify which trips are essential in their daily life, and decide which travel mode corresponds best to their needs and capacities. Various strategic or tactical adaptation behaviors for safer driving are discussed with the participants, such as the use of family, friends, associative and municipal resources, alternative transport options and strategies for avoiding risky situations. This workshop will be adapted to each dyad with a list of alternatives depending on the dyad's living place.

The interventions will be standardized, and each center will be provided with a kit containing an educational guide with the specific objectives of each workshop, the key messages, the facilitation techniques to be used, with detailed instructions, the duration of each activity in each workshop and the tools needed during the workshop. An explanatory workshop will take place for all participating health-care professionals before the start of the study. Moreover, to be involved in the workshop, professionals must be trained as a group facilitator and must have at least 3 years' experience in geriatric units.

#### Control group

participants and caregivers included in the non-experimental group will receive the conventional recommendations for driving a car. These will be provided by their physician during a consultation in the memory clinic, either when they are given their diagnosis or during a follow-up visit. These recommendations consist of a description of the participant's cognitive and sensorimotor risk factors for driving, advice on ways to adapt driving, or a recommendation to stop driving. Information about the procedure involved in responding to a certified physician is also provided.

### Outcomes and assessment tools

#### Main outcome: Implementation of self-regulation strategies

The main outcome is the implementation of self-regulation strategies in driving. Self-regulation strategies will be measured by the participants' scores on the DPPQ “Current Self-Regulatory Practices” subscale (29). The 2-month and 6-month scores of the control group and the experimental group will be compared. The subscale includes eight questions about the frequency of drivers' self-regulation strategies. These strategies consist of: waiting for the rain to stop before driving; asking someone to accompany them rather than driving alone; looking for parking lots to avoid parallel parking; avoiding turning left in traffic; avoiding taking the freeway; avoiding rush-hour traffic; avoiding driving in crowded places; and avoiding driving at night. A four-point scale (0: never, 1: rarely, 2: sometimes, 3: often) reflects the frequency of each item, creating a total score ranging from 0 (never uses any of these strategies) to 24 (uses all strategies often).

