### Aims and hypotheses

A randomized, controlled, single-blind trial will be conducted to assess the impact of the ACCOMPAGNE program on the implementation of self-regulatory strategies in the short and long-term in participants with mild to major cognitive disorders. We hypothesize that participants who benefit from the ACCOMPAGNE program will implement more self-regulatory strategies than those who receive conventional recommendations. The implementation of self-regulatory strategies will be assessed 2 and 6 months after the intervention. Because the objective is to investigate the effects of the ACCOMPAGNE program on the implementation of driving strategies, and the link with awareness of driving difficulties, rather than to examine participants' real driving ability, the driving simulator was chosen over on-road testing. This places drivers in a reproducible and controlled driving environment, and will be used to collect objectives as well as subjective measures of driving ability and self-awareness of this ability. For the same reasons, we will use the differences between the points of view of participants and their natural caregivers to measure the changes after the program.

The secondary objectives are to determine the effects of the ACCOMPAGNE program on (a) self-awareness of driving ability, (b) the mood and quality of life of both participant and natural caregiver, and (c) the natural caregiver's burden. We expect that the ACCOMPAGNE program will (a) increase self-awareness of driving ability (b) maintain participants' mood and quality of life despite any changes made, and (c) maintain the mood and quality of life of natural caregivers, and alleviate their burden to a greater degree than conventional care can.

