### Sample size and data analyses

The self-regulation strategy in driving will be considered beneficial if the score of “Self-Regulatory Practice” increases on average by two points (24) 2 months from inclusion. The number of subjects was computed by considering a Student *t*-test for equal variances between the two groups, with a two-sided alpha risk of 5% and a power of 80%. Based on the sample size calculation, 90 participants per group is considered sufficient to detect differences between the two assessments. Because a 10% loss of dyads is expected during the follow-up period, 100 participants per group will have to be recruited, i.e. a total of 200 participants.

Kolmogorov-Smirnov tests will be used to determine the normality of variables. For demographic, clinical, neuropsychological variables, and scores obtained from scales (e.g., the DPPQ), between-group differences will be examined using Fisher's Exact tests, independent Student *t*-tests or Wilcoxon rank-sum tests, as appropriate. The effect size in the intervention group compared to the control group will be quantified by estimating the difference in mean scores between the 2 groups (experimental vs. control) with a 95% confidence interval. A multiple linear regression model will be performed with DPPQ “Current Self-Regulatory Practices” as the dependent variable, and the level of cognitive impairment at inclusion and other characteristics that may have an effect on the outcome criterion as factors. A mixed-effect linear regression model will also be computed with DHQ, GDS-15, Qol-AD and ZBI as dependents variables, and the group (experimental vs. control) and follow-up time (inclusion, 2 and 6 months) as independent variables. The interaction between the intervention group and the follow-up time will be observed.

The concordance between the performance on the driving simulator and the perception of driving ability measured immediately after simulated driving will be estimated by the Lin concordance correlation coefficient and by the Bland & Altman method for continuous criteria, and by the Cohen Kappa coefficient for ordinal criteria. The number of participants who significantly change their estimation at 2 and 6 months compared to before the intervention will be measured from objective and subjective measures at the different points in time.

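### The main outcome is compared at 2 and 6 months with neither ranked first, but the trial is sized for one 2-month test, and its two-point target is worded as change over time rather than a difference between groups

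*Protocol article*

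**What the plan says.** **Time points.** The section on the main outcome states: "The 2-month and 6-month scores of the control group and the experimental group will be compared". The aims also name both times: "The implementation of self-regulatory strategies will be assessed 2 and 6 months after the intervention". Neither section ranks the two times, splits alpha, or says whether one or both must be positive.

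**Sizing.** The section on sample size and data analyses uses one Student t-test "for equal variances between the two groups", "with a two-sided alpha risk of 5% and a power of 80" per cent. Its only time point is 2 months: the strategy counts as beneficial if the score "increases on average by two points (24) 2 months from inclusion". No comparator appears in that sentence. The section then says that "90 participants per group is considered sufficient to detect differences between the two assessments". On attrition it says: "Because a 10% loss of dyads is expected during the follow-up period, 100 participants per group will have to be recruited".

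**Hypothesis and analysis.** The hypothesis is between groups: programme participants "will implement more self-regulatory strategies than those who receive conventional recommendations". The effect is to be estimated as the difference in mean scores between the arms with a 95% confidence interval. The multiple regression on the DPPQ subscale names no time point. The mixed model over follow-up time lists DHQ, GDS-15, QoL-AD and ZBI, but not the main outcome.

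**The concern.** There are two mismatches, and both concern the primary claim.

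First, two comparisons of the main outcome stand side by side, but alpha and power are set for one. The text does not say what pattern of results makes the trial positive, so the operating characteristics of the primary claim are not fixed.

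Second, the two-point target reads as a before-after change in two separate sentences, while the test and the hypothesis are between groups. The difference matters because the control arm is not inert. The control group section says these dyads are told about the participant's risk factors and how to adapt driving, or are advised to stop. The procedure section places this on the day of inclusion. Some rise in controls is therefore plausible, and a two-point rise in the programme arm would then be a smaller difference between arms.

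**Working it through.** **Inputs from the protocol article:** two-sided alpha 0.05; power 0.80; two-sample t-test with equal variances; target 2 points; 90 evaluable and 100 recruited per group; 10% loss. **Not given:** the SD of the score or of its change, and the correlation between the 2-month and 6-month results. Both are assumptions below.

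**1. The plan's own figures.**
- Attrition: 90 / (1 − 0.10) = 100 per group, 200 in total. This reproduces.
- The 90 cannot be reproduced without an SD. Solving backwards for a between-group difference of 2 points: SD = 2 / [(1.960 + 0.842) × √(2/90)] = 2 / (2.802 × 0.1491) = 4.79. With the t distribution it is 4.76, a standardised effect of 2 / 4.76 = 0.42.
- For scale, SDs of 4, 5 and 6 would need 63, 99 and 142 per group.

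**2. Three readings of the two time points.**

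*Only 2 months is primary.* One test at 5%. Alpha is 5%, power is 80% at the implied SD, and 90/100 per group stands.

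*Either time suffices.* False-positive rate = 1 − P(|Z1| ≤ 1.96 and |Z2| ≤ 1.96), with (Z1, Z2) bivariate normal:

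| Assumed correlation | Rate |
|---|---|
| 0 (bound, 1 − 0.95²) | 9.75% |
| 0.5 | 9.1% |
| 0.7 | 8.3% |
| 0.8 | 7.8% |
| 0.9 | 7.0% |

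A Bonferroni split at 2.5% per time would bring this back to 5%. With SD 4.79 it needs 109 evaluable and 122 recruited per group. At 90 evaluable, power per test is about 71%.

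*Both times required.* Alpha does not exceed 5%. Joint power, with the same 2-point effect and SD at both times, is the bivariate normal probability that both statistics exceed 1.96, each having 80% on its own: 69% at correlation 0.5, 71% at 0.7, 73% at 0.8 and 75% at 0.9.

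**3. What the two points refer to.**

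Suppose two points is the programme arm's rise and controls rise by x. The between-group difference is then 2 − x, and power ≈ Φ[(2 − x) / (SD × √(2/90)) − 1.96], where SD × √(2/90) = 4.79 × 0.1491 = 0.714.
- x = 0: 2 / 0.714 = 2.80, power 80%.
- x = 0.5: 1.5 / 0.714 = 2.10, Φ(0.14) = 56%.
- x = 1: 1 / 0.714 = 1.40, Φ(−0.56) = 29%.

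**4. Was the sizing really before-after?** A paired test within one arm, with SD of change 4.79 (the score SD if baseline and follow-up correlate at 0.5), needs (2.802 × 4.79 / 2)² = 45 participants, or about 47 with the t distribution. That is about half of 90. At this SD the stated number fits a two-sample calculation, which agrees with the named test. It would fit equally well if the two-sample test were run on change from inclusion and 4.76 to 4.79 were the SD of change.

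**The case against.** The strongest reply has four parts.

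**The planned analyses are between groups.** The sizing test, the effect estimate, the comparison in the main outcome section and the hypothesis all compare arms, and no before-after test of the main outcome is planned. A reader might infer that the programme could be declared beneficial with no advantage over control. The documents do not support that: the before-after language is a wording fault in the sample size paragraph, not a planned decision test. This part stands.

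**The 2-month time point may already be primary.** The only section that sets an alpha ties benefit to 2 months. Read that way, 6 months is longer follow-up and 5% holds. A reader might infer that the trial's error rate is above 5%. That follows only if success at either time is enough, which no section says. What remains is that the main outcome section names both times on equal terms, so the 2-month reading must be inferred from the sizing.

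**The SD proves little.** It is back-solved, and it suits a t-test on change scores as well as one on raw scores. A two-sample test on change would reconcile most of the wording. This stands too, but it does not rescue the sentence about differences between assessments.

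**Testing order is commonly left to an analysis plan, which is not shown.** True, and its absence here is not the point. The point is that statements printed in the article disagree with each other. A later plan could set an order, but the article's target and sizing sentences would still need correcting.

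**Conclusion.** The concern holds as an inconsistency in how the primary comparison and its target are stated.

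The 5% and 80% hold together only if the 2-month comparison alone is primary. Otherwise the plan has either a false-positive rate of about 7% to 9% (either time, correlations 0.9 to 0.5) or joint power of about 69% to 75% (both times, correlations 0.5 to 0.9). The correlations are assumed, as is an equal effect at both times for the joint power.

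The two-point target contradicts the between-group test in the same section and the hypothesis in the aims. If it means only the programme arm's rise, a control rise of 0.5 to 1 point lowers power to about 56% to 29%. Those figures rest on the back-solved SD and on an assumed control rise.

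This should be corrected, but it is below must-fix: the planned analyses already compare the arms, and the correction changes neither sample size nor data collection.

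**What to change.** 1. In the main outcome section, name one primary test: the between-group difference in the DPPQ subscale at 2 months, two-sided 5%. Say whether the score or its change from inclusion is analysed.
2. Make the 6-month comparison a key secondary, tested only if the 2-month result is significant.
3. In the sample size section, restate the target as a two-point difference between groups, and give the SD that produced 90 per group.
4. In "90 participants per group is considered sufficient to detect differences between the two assessments", change the last word so that the sentence refers to the two groups.

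An alpha split or requiring both times would also remove the ambiguity. The split needs about 109 evaluable per group by Bonferroni, and requiring both leaves joint power below 80% at 90 per group. Naming 2 months fits the existing sizing and keeps 90/100 per group.

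The cost is a few sentences of wording, and that a difference seen only at 6 months cannot carry the primary claim. The change should be made before any results by arm are seen.
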